### 6.2 Claim 2: IBS and rapport evolve similarly across time

After describing how we will assess the relationship between reciprocal conversational behaviors and IBS, we now turn to the relationship between the psychological state of rapport, as brought about by conversational behaviors, and IBS. To achieve this, we will establish a behavior analysis pipeline that preserves the temporality of the different data streams, while highlighting the relationship among them. Because the time scales of different behavior streams may differ, it can be challenging to analyze the potentially non-linear relationship between rapport and neural synchrony. Here we will therefore set up a pipeline using Dynamic Time Warping (DTW), a powerful method that has been previously used to compare the dynamics of brain activation between the time series of two participants (Azhari et al., 2019). In our own prior work, DTW has also been used to characterize how the conversational strategy usage for each partner in a dyad is aligned in time with that of the other partner (Sinha and Cassell, 2015b), allowing us to assess entrainment, and influence of each member of the dyad on the other. The application of non-linear transformations as carried out by DTW is particularly advantageous for the relatively slow fNIRS time scale compared to the observed behavioral events (Quaresima and Ferrari, 2019). The DTW method causes specific changes in the timing of events in two different data streams. These alterations are made in such a way as to allow for the best possible alignment or matching of the two time-series (Berndt and Clifford, 1994). DTW then provides a measure called “warping distance”, which helps us compare and quantify how different the two sequences are from one another, based on the changes needed to align them. Smaller warping distance values mean that the sequences are more similar, while larger values indicate greater dissimilarity.

To assess the relationship between rapport and IBS, we will therefore calculate the warping distance between IBS and rapport values for each dyad across 30-second intervals. In order to assess the statistical significance of the observed similarity between IBS and rapport curves post-application of DTW, a permutation test will be employed. This involves randomizing the time slices of one of the curves and recalculating the warping distance, repeating this process through 1,000 iterations. The resulting distribution of permuted distances facilitates the determination of a *p*-value, which, when the significance level is set, elucidates whether the observed pattern similarity is statistically significant. Subsequently, a two-way (2 × 7) repeated measures ANOVA can be conducted to explore the effect of experimental phases (collaboration and discussion) and brain regions (left and right PFC, left and right TPJ, left TPJ, left, and right STS) on the resultant warping values. This analysis will enable the assessment of overall differences in warping values attributable to each factor, as well as potential interaction effects between experimental phases and brain regions, providing a clearer understanding of the factors shaping the relationship between rapport and IBS. After having analyzed the relationship between the temporal dynamics of rapport and IBS, we will also run a mediation analysis, where we examine rapport as a mediating factor between reciprocal conversational factors and IBS, to test how conversational factors may influence the dyadic dynamics at both neural and psychological levels. This was the case in prior research where we found that rapport played a mediating role between conversational behaviors and learning gains (Sinha and Cassell, 2015b).

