#### 5.2.2 Inter-brain synchrony

Inter-brain synchrony will be calculated using wavelet transform coherence (WTC), which allows comparison of similarity between signals in terms of spectral content (Czeszumski et al., 2020). WTC calculations will be conducted using the hyperscanning Python pipeline (HyPyP) developed by Ayrolles et al. (2021), across six regions of interest (left and right PFC, left and right TPJ, left, and right STS) within the low-frequency range 0.01 to 0.15 Hz. This range is chosen to filter out respiration and heart rate while still allowing a relatively wide range of frequencies implicated in free verbal interaction in prior work (specifically Mayseless et al., 2019; Nguyen et al., 2021b). Like these previous authors, however, we will carry out visual inspection and spectral analyses and add higher frequencies if motivated by the data.

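### Claim 2 has no test across dyads of whether the IBS-rapport warping distance is smaller than chance; the only comparison with chance works on one pair of curves and ignores serial correlation.

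*Protocol article*

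**What the plan says.** Section 3 and the heading of section 6.2 put Claim 2 as a general statement: neural synchrony and rapport follow similar courses over time. Section 6.2 then sets out three steps.

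1. Distance: "we will therefore calculate the warping distance between IBS and rapport values for each dyad across 30-second intervals".
2. Comparison with chance: "randomizing the time slices of one of the curves and recalculating the warping distance", "repeating this process through 1,000 iterations". The resulting p-value, "when the significance level is set, elucidates whether the observed pattern similarity is statistically significant".
3. Follow-up: "a two-way (2 × 7) repeated measures ANOVA can be conducted to explore the effect of experimental phases (collaboration and discussion) and brain regions". Its stated yield is this: "This analysis will enable the assessment of overall differences in warping values attributable to each factor".

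A mediation analysis comes after these steps and asks a different question. Section 6.2 does not say how results from different dyads combine into a verdict on Claim 2. The ANOVA is labelled 2 × 7 and lists the left TPJ twice, whereas section 5.2.2 works "across six regions of interest (left and right PFC, left and right TPJ, left, and right STS". The two sections need reconciling.

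**The concern.** A claim about dyads in general needs dyads as replicates and chance as the comparator. Step 2 has the comparator without the replication, because it judges one IBS curve against one rapport curve. Step 3 has the replication without the comparator. Neither step answers the question, and nothing links them.

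Whoever analyses the data will have to improvise. The obvious improvisation is to report how many dyads reach significance, and some will do so even if IBS and rapport are unrelated. Section 4.2 plans to analyse and publish the 9–10-year-old band first, so the choice would be made early and on 44 dyads.

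There is a second problem inside step 2. Rapport and IBS in consecutive 30-second epochs are likely to be serially correlated. Shuffled curves are rougher than real ones, and two unrelated smooth curves can be warped onto each other more easily than a rough curve onto a smooth one. The shuffle may therefore make unrelated curves look similar.

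**Working it through.** **Inputs.** 176 dyads, 44 per age band, alpha 0.05 (section 4.1). Two interactive phases and 1,000 shuffles (6.2). Six regions (5.2.2). Curves of 16 to 20 points per phase (5.4). The article gives no error rate or test count for Claim 2, so there is no figure of its own to reproduce. The 176 is taken as given; it was derived for an ANOVA on age groups and measurements, not for this claim.

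**What the ANOVA tests.** Write the expected raw distance in cell c (phase by region) as E[d_c] = μ_c + δ_c. Here μ_c is the distance expected for unrelated curves and δ_c is the departure from it. Claim 2 says δ_c < 0. The ANOVA tests whether μ_c + δ_c is the same in all cells.
- If μ_c is constant and δ_c is equally negative everywhere, Claim 2 is true and the ANOVA is null.
- If δ_c = 0 everywhere but μ_c differs (for example, IBS is smoother in one region), Claim 2 is false and the ANOVA can be significant.

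So its result does not bear on Claim 2 in either direction.

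**What dyad-level p-values would give under no association**, for one region, phase and week, taking each test as valid:
- 176 dyads: expected below 0.05 = 176 × 0.05 = 8.8. The central 95% of Binomial(176, 0.05) is 4 to 15. P(at least one) = 1 − 0.95^176 = 0.9999.
- 44 dyads: expected 44 × 0.05 = 2.2. P(at least one) = 1 − 0.95^44 = 0.895.

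**Validity of the shuffle.** I simulated 17,600 pairs of independent, standardised AR(1) curves of 18 points, with 199 null draws per pair. A distance was called significant when its one-sided permutation p was at most 0.05. The autocorrelations are assumptions; the article gives none.

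| Lag-1 correlation | Error, time-slice shuffle | Error, false-dyad null |
|---|---|---|
| 0 | 4.8% | 5.0% |
| 0.3 | 7.5% | 5.2% |
| 0.6 | 14.4% | 5.0% |

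The false-dyad null pairs one dyad's first curve with other dyads' second curves.

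**Why the null must change before pooling.** At 0.6, distances standardised by the shuffle had mean −0.16 and SD 1.42 although the curves were independent. A one-sided one-sample test of their mean at 5% rejected in about 44% of samples of 176 dyads and 19% of samples of 44. With the false-dyad null the mean was 0.01, and rejection was about 4% and 5%.

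**What a group test can detect.** With the SD of the standardised distance near 1, a two-sided 5% test has 80% power for a mean shift of (1.960 + 0.842)/√176 = 0.21 SD, or 2.802/√44 = 0.42 SD with one age band.

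**The case against.** Section 6.2 does use dyads as replicates, in the ANOVA, so it would be wrong to say that nothing is tested across dyads. That stands: what is missing is a test across dyads against chance.

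A reader might infer that the plan produces thousands of unadjusted p-values. Crossing 176 dyads with 6 regions and 2 phases gives 176 × 6 × 2 = 2,112 cells for one week, or 12,672 over six weeks. The text does not state this. It calls the distance a per-dyad quantity but speaks of a p-value in the singular and does not mention weeks. The wording could even be stretched to one permutation of a mean distance, though no mean over dyads is mentioned. That no adjustment is named for Claim 2 is silence. FDR appears only in section 6.6, and multiplicity detail may sit in an analysis plan not shown. Neither the large counts nor the lack of adjustment is relied on here.

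A reader might also take the feasibility study as proof that selected dyads will be put forward as evidence. Section 9 does show time warping for one dyad, but for smiles against IBS and without a p-value, and section 10 says the sample is too small for conclusions. It does not show what the main study would do.

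Finally, an article may leave pooling to a fuller plan. But this one names the test, the iterations and the follow-up model. The fault lies in what those stated steps can answer, not only in what is left out.

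**Conclusion.** The point holds in this limited form. Followed as written, section 6.2 tests single curve pairs against chance and tests dyads collectively only for differences between phases and regions. No stated analysis decides Claim 2, one of six headline claims.

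If dyad-level p-values filled the gap, about 9 of 176 (4 to 15) would be significant by chance in one region, phase and week, assuming valid and independent tests. Wider counts depend on how many cells are tested, which is not stated.

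The p-values may also be too small. The size depends on an autocorrelation that the article does not give: from no inflation at 0 to about 14% error at 0.6. The real curves should be checked for this.

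**What to change.** State one deciding analysis for Claim 2.

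1. For each dyad and session, standardise the observed warping distance by the mean and SD of a null that keeps serial structure. One option is to pair the dyad's IBS curve with rapport curves of other dyads from the same phase, which adapts the false-dyad idea in section 5.2.2. The other is circular shifts of one curve. With 16 to 20 points there are only 15 to 19 distinct shifts, which suits standardising better than dyad-level p-values.
2. Average the standardised values over sessions within dyad.
3. Test the mean across dyads against that null, with the dyad as unit, in one region and phase named before the data are seen.
4. Treat the other regions and phases as a secondary family under FDR control.
5. Use the standardised distance, not the raw one, in the phase-by-region ANOVA, with the number of regions reconciled with section 5.2.2.
6. Report dyad-level p-values descriptively.

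The change needs no new data. It costs slightly more analysis work and should be settled before the first age band is analysed. The downside is that single-dyad p-values can no longer be cited in support of Claim 2.

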### 4.1 Target population and sample

An *a priori* power analysis was conducted using G^*^Power 3.1.9.7 (Faul et al., 2007) to determine the sample size needed for the study. The analysis was based on an ANOVA with 4 age groups and 6 measurements, using an effect size of (d = 0.24), based on our pilot study results, and an alpha of 0.05. The results indicate that a total sample size of 176 dyads will be required to achieve a power of 0.95. This aligns with the recommendation of Bizzego et al. (2022), who suggested a minimum sample size of *N* = 150 to detect significant IBS. There are significant challenges in recruiting participants for hyperscanning experiments, and particularly for recruiting dyads of unfamiliar children. In the event of a smaller sample size, we can adopt an analytical approach, such as the non-parametric bootstrap test with a pooled resampling method, as proposed by Dwivedi et al. (2017), and cited in Bizzego et al. (2022), which has demonstrated satisfactory performance in cases of small sample sizes and non-normally distributed data. We will enlist equal numbers of dyads from 4 age groups: 5–6, 7–8, 9–10, and 11–12 years (44 dyads per group). As social interaction may differ between boys and girls at these ages (Underwood et al., 1999), dyads will be of the same gender (both boys or both girls), and half of our participants will be male and half female (88 dyads of girls and 88 dyads of boys). As described above, in order to assess the initial building of rapport, all children will be strangers to one another. Our videoconference set-up will facilitate this, as we will set up video-conferencing in 2 different schools or after-school programs.

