For each dyad, we will obtain IBS values for each 30 second epoch and each ROI pair. We will also compute the average IBS across each 8–10 min phase of the experiment. In total, we will thereby obtain IBS values for each dyad, from each ROI, for the entire phase and for each 30-second epoch within that phase. To best capture the IBS evoked by social interaction, we normalize the values of the social phase by computing a Z-score, i.e., removing the average value of the solo phase and dividing by the standard deviation. This process is repeated for each dyad. To compare the difference between phases, then, we run a general linear model (GLM). Normalized IBS values are entered as the dependent variable with interactive phases (i.e., collaboration and discussion) and the interaction effect of ROIs (six per dyad) as fixed factors. To assess whether the observed neural activity is most likely due to exchanges between the children, as opposed to being primarily driven by the content of the task, we will also generate random pairings by calculating IBS with false dyads (the child's time-series paired to the time-series of another child coming from a different dyad during the same phase). We will create multiple such random pairs to generate the distribution of IBS expected under the null hypothesis (H0) (Nguyen et al., 2021a). The values of the actual real pairs will then be compared to these H0 distributions, thus providing an empirical *p*-value. An example of this analysis is illustrated for the feasibility study in Figure 5B. We will also generate a more conservative intra-pair comparison based on temporally shuffled behavior. In this case, the participants stay the same but the epochs are randomized to generate false dyads (Ayrolles et al., 2021).

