While we sometimes refer to feeling instantly “in sync” with somebody we have just met, for the most part rapport fundamentally has to do with the change of a relationship over time. In order to assess the changes in rapport over the course of the 6 weeks of the longitudinal experiment, we will rely on the concept of utopy (Sinha, 2016). Prior work has shown that statistical summaries such as a measure of central tendency or proportion of high and low ratings of rapport, collapse the temporal dimension and are not as robust as more stochastic-based models which capture the evolution of rapport over time (Sinha, 2016). We will thus fit a Markov chain of order 1 to the sequence of 16 to 20 rapport ratings for each session (8–10 min), the sequence of 32 to 40 rapport ratings over the two dyadic sessions (collaboration and open-ended chat) and the 192 to 240 rapport ratings for the two dyadic sessions over the entire 6 weeks, and use the resulting transition probability matrix to generate a measure of the “utopy,” or likelihood of the dyad being in a high-rapport state. This likelihood is calculated as the sum of each transition probability weighted by the distance of the transition (Sinha, 2016; Madaio et al., 2017b). This allows us to assess the temporal dynamics of rapport.

As described above, we will also ask children after each interaction to rate their preferred closeness and feelings of closeness to their partner.

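### The Claim 2 permutation test shuffles 30-second slices freely, so if both series are autocorrelated it can call unrelated IBS and rapport curves similar more often than its nominal level

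*Protocol article*

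**What the plan says.** Section 6.2 of the protocol article will "calculate the warping distance between IBS and rapport values for each dyad across 30-second intervals". A small distance counts as similarity. The reference distribution is a free shuffle of slices: "This involves randomizing the time slices of one of the curves and recalculating the warping distance, repeating this process through 1,000 iterations". The resulting p-value is the one "which, when the significance level is set, elucidates whether the observed pattern similarity is statistically significant". The level itself is not fixed there; the only stated level is in the power analysis of section 4.1 ("and an alpha of 0.05").

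Two other places bear on this test:

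- Section 5.4 (rapport estimation) will "fit a Markov chain of order 1 to the sequence of 16 to 20 rapport ratings for each session". It also uses "the sequence of 32 to 40 rapport ratings over the two dyadic sessions" and a six-week series of 192 to 240 ratings.
- Section 5.2.2 builds a null from false dyads, pairing a child's series with the "time-series of another child coming from a different dyad during the same phase". That null is specified for the level of IBS. Section 6.2 does not apply it to the warping distance.

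**The concern.** A free shuffle answers whether the slices of a curve could have come in any order. Claim 2 asks something else: whether two ordered curves follow each other. The two questions coincide only when slices are exchangeable in time.

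The plan's own account points away from exchangeability. Claims 2 and 5 describe IBS and rapport as changing within a session and over weeks, and section 5.2.1 introduces the epochs in order to see IBS change.

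Dynamic time warping sharpens the problem. It may match one slice to several neighbours, so two slow but unrelated curves can be stretched onto each other cheaply, while a reshuffled, jagged curve cannot. The observed distance then looks small against the shuffled ones whether or not the curves are related.

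At stake is the only significance test stated for curve similarity under Claim 2. Section 4.2 says that the 9–10-year-old data will be analysed and published first, so the null should be settled before that analysis.

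**Working it through.** The documents state no error rate for this test, so there is no figure of the plan's to reproduce. The check is a simulation under the null hypothesis that the two curves are unrelated.

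**Inputs from the documents**
- One phase has 16 to 20 slices (18 used). Two phases of one week have 32 to 40 (36 used). Six weeks have 192 to 240 (216 used). All are from section 5.4.
- One curve is shuffled slice by slice about 1,000 times (section 6.2).

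**Assumptions**
- The lag-1 autocorrelation r of the slice values is not given. It is taken as 0 to 0.8, equal in both series unless stated.
- The level is 5%, since section 6.2 leaves it open.

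**Method.** Two independent first-order autoregressive series were generated and z-scored, and the warping distance was computed with absolute cost. One series was shuffled P = 999 times:

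p = (1 + number of shuffled distances ≤ observed distance) / (P + 1), reject if p ≤ 0.05.

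There were 2,000 data sets at 18 slices and 1,000 at 36. The Monte Carlo standard error at a rate of 14.4% with 2,000 data sets is √(0.144 × 0.856 / 2000) ≈ 0.8 percentage points. At 26.2% with 1,000 data sets it is √(0.262 × 0.738 / 1000) ≈ 1.4 points.

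**False-positive rate of the slice shuffle**

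| r in both series | 0 | 0.2 | 0.4 | 0.5 | 0.6 | 0.8 |
|---|---|---|---|---|---|---|
| 18 slices | 5.0% | 5.8% | 7.8% | 10.7% | 14.4% | 24.3% |
| 36 slices | 5.7% | 6.0% | 14.3% | 16.8% | 26.2% | 41.2% |

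The first column confirms that the test holds its level when slices are independent, so serial dependence causes the rest. A separate simulation gave about 12% at r = 0.5 with 18 slices, hence the range of 8–12% for r = 0.4–0.5. A coarse run at 216 slices (99 shuffles, 200 data sets) gave 15.5% at r = 0.2, 49% at 0.4 and 92.5% at 0.6. It treats six weeks as one unbroken stationary series, so it shows direction only.

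**Sensitivity at 18 slices**
- r = 0.6 in one series and none in the other: 5.1% or 4.5%, depending on which is shuffled.
- Min-max scaling at r = 0.4 / 0.6 / 0.8: 10.1 / 14.3 / 21.6%.
- Warping limited to ±3 slices, same r: 8.3 / 13.0 / 20.1%.
- Rapport as the mean of three 1–7 ratings, same r: 9.3 / 13.0 / 17.0%.
- Unrelated linear drifts of random sign, with a total rise of 2 or 3 noise standard deviations: 17% and 36%.

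**Nulls that keep slice order**, at r = 0 / 0.4 / 0.6 / 0.8
- One dyad's IBS against the intact rapport curves of 175 other dyads: 4.5 / 4.2 / 4.5 / 6.1% (18 slices) and 4.1 / 5.2 / 5.2 / 4.6% (36 slices).
- Circular shifts within the dyad: 5.3 / 4.9 / 5.7 / 7.5% (20 slices) and 4.6 / 5.5 / 5.1 / 7.4% (40 slices).

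**The case against.** The strongest reply is that the size of the error rests on a quantity the documents never give. An order-1 Markov fit does not prove dependence, since an independent sequence is a special case of it. Section 5.4 has slices rated in random order, which removes rater carry-over, and single-slice ratings add noise. Section 5.2.2 computes IBS over 0.01–0.15 Hz, and every component above 1/30 ≈ 0.033 Hz has a period shorter than one slice. With weak dependence, or dependence in one series only, the test is close to nominal. All of this stands, and it is why the size is given as a range. It does not rescue the null: the slowest IBS components have periods of 100 s, more than three slices, and slow change in both series is what Claims 2 and 5 expect.

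Three stronger readings are tempting but unsupported:

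- **That the error carries into the analysis of variance on warping values.** That analysis uses the distances themselves, not the permutation p-values, so the choice of null neither harms nor repairs it.
- **That an even larger group-level error follows.** Section 6.2 specifies no test of the mean distance over dyads, so no error rate for one can be charged to the plan.
- **That the plan implies one test per dyad, region, phase and week.** The text fixes only the dyad as the unit. A weekly split is not stated, so no total count of p-values follows.

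A last objection is that false-dyad pairing narrows the hypothesis. This is correct and must be disclosed with the change.

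**Conclusion.** The concern holds in conditional form. Section 6.2 fixes a null that ignores serial order, and nothing else in the article replaces it for the warping distance. With at least moderate autocorrelation in both series, the false-positive rate in a single phase runs from about one and a half times nominal (7.8 / 5 ≈ 1.6 at r = 0.4) to about five times (24.3 / 5 ≈ 4.9 at r = 0.8). Over two phases it reaches about eight times (41.2 / 5 ≈ 8.2). At r of 0.2 or below with one or two phases, or with dependence in one series only, the inflation is slight or absent. These figures assume equal first-order dependence, a 5% level and the series lengths of section 5.4. A reader might infer that the test is badly inflated in every case; the documents do not support that, because they report no autocorrelation for either series.

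**What to change.** Replace the slice shuffle in section 6.2 with a null that keeps each curve in its original order. The preferred version extends the false-dyad idea of section 5.2.2: warp each dyad's IBS curve onto the intact rapport curves of other dyads from the same age group, week and phase, with the same scaling and a common length, and compare the dyad's own distance with that distribution. State the significance level in the same paragraph.

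Two consequences should be written down:

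- The test then addresses correspondence specific to the dyad. If IBS and rapport rise together in every dyad, re-pairing absorbs that shared trajectory. If the shared rise is of interest, it needs its own analysis.
- With 44 dyads per age group (section 4.1), each dyad has 43 comparison curves, so its smallest possible p-value is 1/44 ≈ 0.023.

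Circular shifts of one curve within the dyad are an alternative and held about 5–7.5%. However, n slices give only n positions, so the smallest p-value is 1/18 ≈ 0.056 at 18 slices and 1/20 = 0.05 at 20. A single phase therefore barely reaches the 5% level, if at all, and this option suits the longer series.

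The cost is one paragraph and modest recoding, with no new data. Fewer single-dyad results may be nominally significant. The change should precede analysis of the 9–10-year-old data.

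### Section 6.2 compares warping distances between phases without fixing a common number of epochs, so any difference in mean phase length would be read as a phase effect

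*Protocol article*

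**What the plan says.** Section 6.2 will "calculate the warping distance between IBS and rapport values for each dyad across 30-second intervals". It tests each observed distance by permuting the time slices of one curve. A repeated-measures ANOVA may then follow, to "explore the effect of experimental phases (collaboration and discussion) and brain regions" "on the resultant warping values". What enters that model is the distance itself, not a permutation p-value or a score standardised against the permutations. Differences are to be attributed to phase, region and their interaction.

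The section reads the distance directly: "Smaller warping distance values mean that the sequences are more similar, while larger values indicate greater dissimilarity". It does not mention series length.

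On length, section 5.2.2 says "We will also compute the average IBS across each 8–10 min phase of the experiment", and section 5.4 speaks of "the sequence of 16 to 20 rapport ratings for each session". Section 5.4 applies the same range to both dyadic sessions, collaboration and chat. The task description in section 4.2 gives 8–10 min for the chat and no separate duration for collaboration.

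**The concern.** In standard dynamic time warping the distance is a cost added up along the alignment path. A longer pair of series has a longer path and so a larger total, even when the two curves are related in exactly the same way. Scaling each curve beforehand does not remove this.

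The ANOVA compares this total between collaboration and discussion. If one phase tends to run longer, its distances are larger and it is reported as the phase where rapport and synchrony agree less. The two phases also end differently. Collaboration works towards a joint list of claims and evidence, while the chat fills a set interval, so a gap in mean length is plausible. At stake is the conclusion about which kind of interaction ties rapport and synchrony more closely.

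**Working it through.** **1. The plan's own figure.** Epochs per phase = minutes × 60 / 30. This gives 8 × 60 / 30 = 16 and 10 × 60 / 30 = 20. Two dyadic sessions give 32 to 40, and six weeks give 192 to 240. All agree with section 5.4. The longest phase has 20/16 = 1.25 times the epochs of the shortest.

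**2. Inputs.** From the article: 16–20 epochs; 176 dyads in total and 44 per age group (section 4.1). The figure of 44 matters because one age group is to be collected and published first (end of section 4.2). Assumptions, because the article is silent: absolute-difference cost; unrelated series, so the true relation is the same in both phases; autocorrelation (AR(1)) 0 or 0.5; z-score or min-max scaling; one region and one session per dyad; paired test at two-sided 0.05.

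**3. Growth with length** (20,000 simulated pairs per length):

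| Scaling, autocorrelation | Mean at 16 | Mean at 20 | Growth | SD |
|---|---|---|---|---|
| z-score, 0 | 11.93 | 14.48 | 21% | 1.78–1.88 |
| z-score, 0.5 | 12.13 | 14.57 | 20% | 2.44–2.61 |
| min-max, 0 | 3.45 | 4.02 | 17% | 0.63–0.66 |
| min-max, 0.5 | 3.51 | 4.06 | 16% | 0.81–0.85 |

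**4. False phase effects by formula.** With a mean step d per epoch and SD s in each phase, the paired test has noncentrality d√N / (s√2), and the rejection rate is about Φ(noncentrality − 1.96).

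- z-score, 0.5: d = (14.57 − 12.13)/4 = 0.61 and s ≈ 2.53. At N = 176 the noncentrality is 0.61 × 13.27 / 3.58 = 2.26, giving about 62%. At N = 44 it is 1.13, giving about 20%.
- min-max, 0.5: d = (4.06 − 3.51)/4 = 0.1375 and s ≈ 0.83. At N = 176 it is 1.55, about 34%. At N = 44 it is 0.78, about 12%.

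**5. False phase effects by simulation** (2,000 studies per setting; ranges are over different starting lengths):

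| Scaling, autocorrelation | 1 epoch, N=176 | 1 epoch, N=44 | 2 epochs, N=176 | 2 epochs, N=44 |
|---|---|---|---|---|
| z-score, 0 | 88–93% | 34–38% | 100% | 87–89% |
| z-score, 0.5 | 60–67% | 19–22% | 99% | 59–61% |
| min-max, 0 | 44–60% | 14–19% | 97–99% | 49–56% |
| min-max, 0.5 | 33–38% | 12–13% | 85–87% | 33–34% |

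Smaller pools of simulated pairs widen these to about 27–93% and 11–40% for one epoch, and 78–100% and 27–90% for two. With 1,000 pairs per length, the standard error of the mean step is about 2.5 × √(2/1000) = 0.11 against a step near 0.6. The wider ranges are the ones quoted in the conclusion.

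**6. Controls.** With 18 epochs in both phases, the rejection rate is about 5%. With lengths drawn at random from 16–20 in both phases, it is 4–7%. So varying length adds noise, but no bias unless the means differ.

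**7. Do common adjustments cure it?** Dividing by path length overcorrects: from 16 to 20 epochs the adjusted mean falls by about 3–10%. At 16 versus 20 epochs and 176 dyads the phase test still rejects in about 62–99% of studies, and at a two-epoch gap in about 18–59%. Standardising against shuffled surrogates of the same length gave 4–5% without autocorrelation. With autocorrelation 0.5 and 16 versus 20 epochs, it gave 8% (44 dyads) and 14% (176 dyads).

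**The case against.** The strongest reply is that the article gives both phases the same 8–10 min range and nowhere says that one runs longer. That stands. A reader might infer that variable duration alone creates a phase effect, or that collaboration has no time limit because section 4.2 gives it none. Neither is supported: sections 5.2.2 and 5.4 cover collaboration too, and with equal length distributions the error rate stays near 5%.

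A reader might also infer that younger dyads who stop sooner would produce a phase effect. They would not. The comparison is within dyad, the ANOVA has no age factor, and a dyad that is short in both phases contributes no phase difference.

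Nor does the point reach Claim 2's main test. The permutation p-value compares series of equal length, and regions within a phase share one length. The ANOVA is worded as optional and exploratory.

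Finally, the article does not say the distance is unadjusted, and a condensed article may leave such detail to a fuller plan. That limits the weight of the point but does not remove it. The article does fix the outcome, its reading and the model, and the adjustment an analyst would most readily reach for, division by path length, does not reliably solve the problem.

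**Conclusion.** The point holds in a conditional form. As described, the ANOVA cannot separate lower similarity from longer duration when mean phase lengths differ. A mean gap of 30 seconds would give a false phase effect in roughly 27–93% of studies of 176 dyads and 11–40% of 44. A gap of one minute would give roughly 78–100% and 27–90%. These rates assume a cumulative absolute-difference cost, one region and one session per dyad, and the scalings and autocorrelations shown. The size varies widely with those choices, but the direction was the same in every setting. Without a gap in means there is no bias. Because the gap is unknown, only the phase comparison is exposed, and that analysis is exploratory, this is a should-fix.

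**What to change.** Add one sentence to section 6.2: the warping distances entered in the ANOVA are computed on the same number of epochs in both phases, for example the first 16, which every 8-min phase contains. Equal lengths restored the nominal error rate in every setting tried.

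Do not rely on division by path length. Standardising each distance against surrogates of the same length is an alternative only if the surrogates preserve autocorrelation; plain shuffling does not.

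The cost is a few lines of code and up to 4 of 20 epochs, dropped from this one analysis. Data collection and the permutation test stay as they are.
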